**Methods/Designs:**

Our goal is to test the hypothesis that patients with painful osteoporotic vertebral compression fractures who undergo vertebroplasty have less disability and pain at 1 month than patients who undergo a control intervention. The control intervention is placement of local anesthesia near the fracture, without placement of cement. One hundred sixty-six patients with painful osteoporotic vertebral compression fractures will be recruited over 5 years from US and foreign sites performing the vertebroplasty procedure. We will exclude patients with malignant tumor deposit (multiple myeloma), tumor mass or tumor extension into the epidural space at the level of the fracture.

We will randomly assign participants to receive either vertebroplasty or the control intervention.

Subjects will complete a battery of validated, standardized measures of pain, functional disability, and health related quality of life at baseline and at post-randomization time points (days 1, 2, 3, and 14, and months 1, 3, 6, and 12). Both subjects and research interviewers performing the follow-up assessments will be blinded to the randomization assignment. Subjects will have a clinic visit at months 1 and 12. Spine X-rays will be obtained at the end of the study (month 12) to determine subsequent fracture rates. Our co-primary outcomes are the modified Roland score and pain numerical rating scale at 1 month.

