### Baseline assessment

All subjects will complete baseline assessments prior to the randomized treatment assignment. Subjects will provide the study with spine images (either plain film X-ray or MRI) to document the fracture(s). The research coordinator will complete a chart review to obtain pertinent health variables, including height and weight, prior osteoporotic fractures and back procedures, osteoporosis history, current and historical osteoporosis therapy and oral corticosteroid use, and current medication for back pain. Subjects will complete a battery of standardized measures of pain, physical disability and health related quality of life, as well as comorbidities, back pain medications and demographics. A brief physical examination will be performed, including blood pressure and brief neurological assessment (motor system, sensation, reflexes, and straight leg raises).

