For primary analyses, an "intention-to-treat" strategy will be employed, such that each subject is analyzed in the group to which he or she is randomized, regardless of actual compliance with the intended intervention. This strategy requires minimal assumptions and maintains the random allocation, although intervention effects may be "diluted" if cross over between procedures is high. We will stratify all analyses for site. Non-adherence and/or dropout complicate analysis of follow-up data. Consideration of missing data is essential to characterize the potential for selection bias through attrition. When appropriate, missing follow-up data for subjects who withdraw will be imputed.

The primary outcomes of Roland and pain measure will be assessed at the one-month time point. This allows adequate time for any intervention benefit to manifest, and is the final assessment prior to the opportunity to select further treatment (crossover). The primary analysis will test for the efficacy of vertebroplasty using a permutation test based on the randomization distribution. Such analysis allows formal inference relying solely on the random assignment of subjects for validity (i.e., makes no additional statistical assumptions). Confidence intervals for the magnitude of treatment effect will be obtained using linear regression with a treatment indicator as the predictor of interest and using dummy variables to stratify on site. We will perform a similar analysis using the 0–10 numerical pain rating scale at one month. Secondary analyses will describe the complete time profile for the Roland and the pain ratings through one year using methods appropriate for the analysis of repeated measures [16].

In addition to hypothesis tests based on the randomization scheme, we will conduct secondary analyses that adjust for important baseline characteristics, such as baseline pain severity, and functional status. We will conduct limited exploratory analyses to assess evidence for differential treatment response by subject subgroups by testing treatment-covariate interactions for factors that are specified *a priori *in a detailed analysis plan to be created prior to data analysis. We will also perform a subgroup analysis examining whether enrolling early or late in the study had an effect on outcome. This will help determine if a significant learning curve was present and, if so, the magnitude of the effect.

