### Sample Size

In unpublished pilot data on 88 patients, we found an 8.6 point average reduction on the Roland (standard deviation of 6.7) at 4 weeks following the vertebroplasty procedure. We originally planned to enroll 249 subjects but had to adjust our expectations to 166 subjects due to difficulty with enrolment. With at least 90% follow-up at one month, we expect to have 75 subjects in each arm (150 total) assessed. This sample size yields 95% power to detect a 4-point effect size, and maintains good power for a 3-point effect size (78% power).

We will use a 0–10 numerical pain rating scale to test the hypothesis that short and long-term pain relief is greater in the percutaneous vertebroplasty group than in the control group. In a pilot study, we found a mean reduction of 7.1 (2.7 SD) points on this pain rating scale in a group of patients who received vertebroplasty [24]. A sample size of 150 has greater than 95% power to detect an effect size of 1.75 and a greater than 80% power to detect a 1.25-point effect size.

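### The primary confidence-interval model leaves out the baseline scores the trial collects, and the power figures rest on change-score SDs that match an analysis of 1-month scores only in special cases

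*Protocol article*

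**What the plan says.** The Abstract sets the endpoints: "Our co-primary outcomes are the modified Roland score and pain numerical rating scale at 1 month". They are worded as scores at a time point, not as changes from baseline.

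The Analysis section sets the primary inference: "The primary analysis will test for the efficacy of vertebroplasty using a permutation test based on the randomization distribution". The permutation statistic is not spelled out. The confidence interval comes from "linear regression with a treatment indicator as the predictor of interest and using dummy variables to stratify on site", and the pain rating is to be handled in a similar way. Baseline enters at the next level down: "we will conduct secondary analyses that adjust for important baseline characteristics, such as baseline pain severity, and functional status".

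The values needed for adjustment will exist for everyone, according to the Baseline assessment section: "All subjects will complete baseline assessments prior to the randomized treatment assignment".

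The Sample Size section gives two SDs, both from treated pilot patients and both for pre-post reduction. For Roland, "we found an 8.6 point average reduction on the Roland (standard deviation of 6.7) at 4 weeks". For pain, "we found a mean reduction of 7.1 (2.7 SD) points on this pain rating scale". With 75 assessed per arm it states 95% power for 4 Roland points, 78% for 3 points, over 95% for 1.75 pain points and over 80% for 1.25. The Discussion lowers enrolment to 100 with 90% follow-up and states 80% power for 4 Roland points and 87% for 1.75 pain points.

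**The concern.** There are two linked issues.

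First, a Roland or pain score measured before randomization is usually correlated with the same score a month later. A model with treatment and site only leaves that explained variation in the residual, so the interval is wider than it need be. Planned enrolment has fallen from 249 to 166 to 100, so precision is scarce.

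Second, power was computed with the SD of a within-patient change, while the primary outcome reads as a 1-month score. These are different quantities. If the 1-month score varies more than the change does, the 80% and 87% in the Discussion are too high for the planned analysis. If it varies less, they are too low. The article does not give what is needed to tell which.

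**Working it through.** **Inputs.** SD of reduction 6.7 (Roland) and 2.7 (pain), from Sample Size. Analysed subjects per arm: 75 (Sample Size), and 100 × 0.9 / 2 = 45 (Discussion). Alpha and sidedness are not stated. Two-sided 0.05 is assumed because it returns the stated figures; one-sided 0.05 would give about 86% for 3 Roland points, not 78%.

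**Step 1: reproduce the stated powers.** SE = SD × √(2/n), with power from the normal approximation / noncentral t.

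| Outcome, n per arm | SE | Difference / SE | Power | Stated |
|---|---|---|---|---|
| Roland 4 points, 75 | 1.094 | 3.656 | 95.5% / 95.3% | 95% |
| Roland 3 points, 75 | 1.094 | 2.742 | 78.3% / 77.8% | 78% |
| Pain 1.75 points, 75 | 0.441 | 3.969 | 97.8% / 97.6% | >95% |
| Pain 1.25 points, 75 | 0.441 | 2.835 | 80.9% / 80.4% | >80% |
| Roland 4 points, 45 | 1.412 | 2.832 | 80.8% / 80.0% | 80% |
| Pain 1.75 points, 45 | 0.569 | 3.074 | 86.8% / 86.0% | 87% |

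The arithmetic is right on its own inputs, and the stated powers are consistent with using the change-score SDs.

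**Step 2: when does the change SD equal the 1-month SD?** Let SD0 and SD1 be the baseline and 1-month SDs and r their correlation. Then SD_change² = SD0² + SD1² − 2·r·SD0·SD1. With SD0 = SD1, this gives SD1 = SD_change / √(2(1 − r)). The two agree at r = 0.5. SD1 is smaller below 0.5 and larger above it.

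**Step 3: what baseline adjustment does, for any r.** For a fixed baseline slope b, the residual variance is SD1² − 2·b·r·SD0·SD1 + b²·SD0². The raw-score analysis sets b = 0 and the change-score analysis sets b = 1. ANCOVA uses the minimising slope b = r·SD1/SD0, which leaves SD1²(1 − r²). That cannot exceed either of the other two, apart from one degree of freedom. It equals the raw-score variance when r = 0 and the change-score variance when the slope is 1 (r = SD0/SD1).

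**Step 4: illustrative size.** r is not in the article, so a range is assumed, with equal variances, change SD fixed and 45 per arm. Under these assumptions the ANCOVA SD is SD_change × √((1 + r)/2). Powers are noncentral t, with one degree of freedom fewer for ANCOVA and those for site ignored.

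| r | Roland SD1 / ANCOVA SD | Power, 4 points: unadjusted vs ANCOVA | Pain SD1 / ANCOVA SD | Power, 1.75 points: unadjusted vs ANCOVA |
|---|---|---|---|---|
| 0.3 | 5.66 / 5.40 | 91% vs 93% | 2.28 / 2.18 | 95% vs 96% |
| 0.5 | 6.70 / 5.80 | 80% vs 90% | 2.70 / 2.34 | 86% vs 94% |
| 0.6 | 7.49 / 5.99 | 71% vs 88% | 3.02 / 2.41 | 78% vs 92% |

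**Step 5: unequal variances.** Entry requires pain of at least 3, and a mean pilot pain reduction of 7.1 on a 0–10 scale means a mean baseline of at least 7.1. Baseline spread may therefore be compressed. Take SD0 = 0.6 × SD1 and r = 0.3 (assumed). Then SD_change² = SD1²(1 + 0.36 − 0.36) = SD1², so the mismatch vanishes. The ANCOVA SD for Roland is 6.7 × √(1 − 0.09) = 6.39, and for pain 2.7 × √0.91 = 2.58. Roland power goes from 80% to 84%, pain from 86% to 89%.

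**The case against.** The strongest reply is that nothing here is an error. The Analysis section justifies its choice: the permutation test draws its validity from randomization alone. Adjusted analyses are declared in advance as secondary, and baseline comparability will be examined. That stands. This is a question of efficiency and planning, not of validity.

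Other parts of the reply also stand:

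- A reader might infer that the primary test itself is fixed as unadjusted. The contrast with the adjusted secondary analyses points that way, but the permutation statistic is not given and an article may leave it to the analysis plan. Only the confidence-interval model is fixed in print.
- A reader might infer that the trial is less well powered than stated. The article does not support a direction. With equal variances the stated power is conservative below r = 0.5, right at 0.5 and optimistic above. If the regressed outcome was meant to be change, the SD mismatch disappears. Adjustment could still gain precision (residual SD 5.80 against 6.7 at r = 0.5).
- A reader might infer that ANCOVA always beats both alternatives. It is never worse in residual variance, but it only ties with the change score when the baseline slope is 1.
- A reader might infer that chance baseline imbalance biases the primary estimate. It does not: such imbalance is already reflected in the permutation distribution and the interval width. No baseline SD is given, so its likely size cannot be worked out from the article.

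What does not stand is the view that the choice is therefore costless. Adjustment can be carried inside a permutation test without giving up the randomization-based validity that the article values.

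**Conclusion.** The point holds as a worthwhile improvement to a valid plan. The printed confidence-interval model leaves out the baseline value of its own outcome, and the power statements use an SD that belongs to a change score.

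The direction of the precision argument rests on Step 3 and needs no assumption about r. Its size does. Over assumed r of 0.3 to 0.6 with equal variances, adjustment adds about 2 to 17 percentage points of power for 4 Roland points and about 1 to 14 for 1.75 pain points. It adds about 3 to 4 points if baseline spread is compressed and r is low. All of these take the SD from a single treated pilot group as applying to both arms. Whether the stated 80% and 87% are too high or too low for an unadjusted 1-month comparison cannot be settled from the article.

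**What to change.** For each co-primary outcome, make the primary regression the 1-month score on treatment, the baseline value of the same scale, and site. Base the permutation test on the same baseline-adjusted statistic, re-randomizing within site and block. Keep the unadjusted analysis as a sensitivity analysis.

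In the Sample Size section and the Discussion, state that 6.7 and 2.7 are SDs of change. Given those SDs, the stated powers then become approximate lower bounds for the adjusted model, whatever r turns out to be.

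No new data are needed. The cost is revising the analysis text and the power statements. The fit with the stopping criteria that the monitoring board has already set for its reviews at 73 and 90 subjects (Safety Monitoring) must also be checked, since those reviews use the same outcomes.

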### Measures

Our primary outcomes are the modified Roland Scale [8] (a measure of back pain-related physical disability) and a 0–10 numerical rating scale of pain intensity (0 = no pain, 10 = pain as bad as could be) [9]. A 2 or 3-point difference on the Roland Scale is the smallest clinically important difference found in studies of patients with other types of back pain [8,10].

Subjects are asked about their use of medications (anti-osteoporosis, analgesic, and steroid) to assess for potential confounding in the outcomes analyses. We will also collect a self-report version of the Charlson comorbidity index [11]. Secondary outcome measures include the modified Deyo-Patrick Pain Frequency and Bothersomeness Scale [12], the SF-36 version 2 (a general health-related quality of life measure) [13], the Strength of Function (SOF) and Activities of Daily Living (ADL), the EQ-5D (a measure of health state preferences) [14], and the Osteoporosis Assessment Questionnaire (OPAQ) body image domain (an osteoporosis-specific functional status instrument) [15].

A back pain resource use questionnaire is used to assess the medical care costs associated with vertebroplasty. Subjects are asked to provide information concerning outpatient and office visits, including the medical specialty of the provider; the number of visits; the tests, treatments, or devices received at the visit; and the average length of time for each visit. Hospitalizations and ambulatory surgery are also recorded in the questionnaire. Finally, we will assess the name, dose, and frequency of use of osteoporosis medications, analgesics, and any other drugs potentially used for back pain.

Adverse events and serious adverse events will be collected at each time point (clinic visit and telephone call). Data acquired at the visits and telephone calls is entered into the electronic database. Any medical problems are "caught" in the electronic system and an automatic e-mail goes to the study principal investigator and the database controller. This facilitates quick action on any serious adverse event. The DSMB and NIAMS are notified of adverse events using KAI, Research Inc. as the intermediary for notification.

Follow up radiographs will be completed for all subjects at the 12 month clinical visit. The study will pay for these x-rays. Adjacent fractures, if there are any, will be able to be seen on these radiographs.

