Stratified 2-group methods will compare the intervention groups on the secondary outcomes at 1-month, and longitudinal analysis using linear mixed models will be used to characterize and compare the time course for the intervention groups. In addition, we will compare the two groups controlling for baseline covariates including study site, demographics, clinical characteristics, and co-morbidities such as including medical and psychological factors.

We will test the hypothesis that vertebroplasty is a cost-effective procedure for reducing pain and dysfunction due to osteoporotic vertebral fractures. We will calculate the costs to health care providers of care in the first year following randomization. We believe that the 12-month time-frame will allow adequate measurement of the important differences in cost and outcome between treatment arms. However, if significant differences persist at one year, we will construct a decision model to extrapolate the results. As an exploratory analysis, we will build a worst-case scenario model that assumes that any benefits of vertebroplasty fall off rapidly over time such that after 5 years benefits are equal between groups. Survival will be based on published studies of mortality amongst an osteoporotic population [17,18]. All costs and benefits beyond one year will be discounted at 3%, according to U.S. guidelines [18].

We will combine utilization information recorded in the resource use questionnaire with unit cost information available for drugs [19], office visits [20], office-based tests and procedures, and hospitalizations [21]. The total cost will exclude the cost of the control procedure, both for subjects initially randomized to this procedure and those who later cross over to the control procedure. The costs of the radiographs necessitated by the study protocol at 12 months post-randomization will also be excluded. Costs to healthcare payers will be combined with the out-of-pocket cost to patients of obtaining health care to calculate the total incremental cost to society of vertebroplasty. All costs will be adjusted to a common year using the medical care component of the consumer price index [18].

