The primary economic outcome measure is the EQ-5D preference score [22]. The EQ-5D assesses three levels of severity (no problems, moderate problems, and extreme problems) across each of five dimensions of health (mobility, self-care, usual activities, pain/discomfort, and anxiety/depression). Responses to the EQ-5D can be converted into a weighted health state index using predetermined values derived from general population surveys [22]. This index is anchored at zero (very severe health status equivalent to death) and one (best imaginable health status). By combining this quality of life index with information on patient survival, a quality adjusted life year (QALY) can be calculated.

We will calculate the incremental net benefit (INB) statistic of vertebroplasty, defined as:

INB = λ(Effect_vertebroplasy _- Effect_control_) - (Cost_vertebroplasty _- Cost_control_),

where λ is the amount that society is willing to pay for an average improvement of one quality adjusted life year. Rather than use one arbitrary cut-off (e.g., $100,000 per QALY) to define cost-effectiveness, we will present the results as a cost-effectiveness acceptability curve (CEAC). The CEAC uses non-parametric bootstrap methods [16] to determine, for any given willingness-to-pay cut-off, the probability that vertebroplasty is cost-effective. CEAC curves enable decision-makers with different budget constraints to judge the cost-effectiveness of interventions in their setting.

In the primary analysis, we will exclude subjects with missing cost or effectiveness data. However, as data may not be missing at random, we will conduct a secondary analysis using multiple imputation methods to estimate missing data [23]. We will use univariate and multivariate sensitivity analysis to estimate which non-stochastic parameters (e.g. unit costs, discount rate) have the greatest influence on our findings.

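### The economic analysis names two different cost perspectives, and the total it calls a cost to society holds only health-care payments

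*Protocol article*

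**What the plan says.** All of this is in the protocol article, Methods/Design.

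- **Analysis, opening of the cost-effectiveness text:** "We will calculate the costs to health care providers of care in the first year following randomization".
- **Analysis, two paragraphs of costing method:** recorded resource use is multiplied by unit costs for drugs, visits, office-based tests and procedures, and hospital stays. Then "Costs to healthcare payers will be combined with the out-of-pocket cost to patients of obtaining health care", in order "to calculate the total incremental cost to society of vertebroplasty". Also, "The total cost will exclude the cost of the control procedure", in whichever arm it is given.
- **Analysis, definition of the INB:** one cost difference between arms, with no perspective named. The multiplier λ "is the amount that society is willing to pay for an average improvement of one quality adjusted life year".
- **Measures:** "A back pain resource use questionnaire is used to assess the medical care costs associated with vertebroplasty". Its items include the number of visits "and the average length of time for each visit".
- **Analysis, sensitivity analyses:** unit costs and the discount rate are the examples given. Perspective is not among them.

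**The concern.** What providers spend to deliver care is not the same quantity as what payers and patients pay for it. The Analysis section states both, and the INB takes a single cost difference without saying which.

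The label attached to the second sum is also wider than its content. Payer costs and patients' own spending on health care are both payments for care. The time that patients give up, and any help from carers, is not part of the sum as defined. The plan nevertheless calls it a cost to society and pairs it with society's valuation of a QALY.

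At stake is the wording of the economic conclusion. The plan intends to test whether vertebroplasty is cost-effective, and the INB and the acceptability curve both rest on this cost term. A result reported as societal would claim more than was calculated. If the perspective is not fixed beforehand, it could also be chosen after the results are seen.

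**Working it through.** The documents state no unit cost, resource-use figure, cost total or INB value, so there is no figure to reproduce. The check sets the statements side by side.

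**1. How many costings are there?** Two. The first is cost to providers. The second is payer cost plus patients' out-of-pocket cost. The cost to society is not a third, because it is the name given to the second sum in the same sentence.

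**2. Which one enters the INB?** The formula does not say. Context favours the second:
- It is the only incremental cost that the section constructs.
- The section describes no method for costing what providers spend.
- λ is framed from society's side, which matches the label on the second sum.

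**3. What does the second sum contain?**

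| Component | Named in the sum? | Related data collected? |
|---|---|---|
| Payers' cost of health care | Yes | Yes, resource use questionnaire |
| Patients' out-of-pocket cost of obtaining care | Yes | Not itemised in the article |
| Patient time at visits | No | Yes, visit counts and average length (Measures) |
| Carer time | No | None named |

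The priced items are all medical care, which agrees with the purpose of the questionnaire given under Measures.

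**4. Where could the two costings diverge?** The control procedure is left out of total cost, and the Crossover section says vertebroplasty is billed to the subject's insurance. The vertebroplasty procedure is therefore likely to be a large part of the cost difference, and it is one place where provider cost and payer payment can differ. This is an inference from the design. No amount is given.

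**5. Scale.** From the plan's formula, INB = λ × (effect difference) − (cost difference). A change of d dollars in the cost difference moves the INB by −d, which is worth d/λ QALYs. At the plan's example of λ = $100,000 per QALY, with assumed values of d:
- d = $500: 500/100,000 = 0.005 QALY per patient
- d = $1,000: 1,000/100,000 = 0.01 QALY per patient
- d = $5,000: 5,000/100,000 = 0.05 QALY per patient

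These lines only convert dollars to QALYs and are not estimates for this trial. The direction is equally open. Counting patient time could raise or lower the cost difference, depending on which arm makes more or longer visits.

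**The case against.** The strongest defence is that only one costing procedure is actually described. The provider sentence leads straight into the reason for a 12-month horizon, so it may be there to set the time frame, with the word for payers chosen loosely. The INB would then use the payer-plus-patient sum, and a reader can see what that sum contains because its components are stated. The article is condensed, so a fuller document may explain how visit time is valued. What a societal cost must include also depends partly on a cited guideline that is not at hand. Most of this stands. It makes the provider wording a small correction and keeps the point minor.

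It does not remove the point. The article does more than stay silent about time: it defines the total by its components and gives that total a name the components do not justify. Disclosing the components helps a careful reader but does not make the headline label right.

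A reader might infer three stronger claims that the documents do not support:
- **Three competing perspectives.** There are two costings, as shown above.
- **Double counting of the patient's share.** This would follow only if the unit costs were full prices that already include it. The unit-cost sources are not available, and the text adds each party's cost once.
- **A demonstrated numerical error in the INB.** Without cost data, no difference between the two costings can be shown.

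**Conclusion.** The point holds as an inconsistency of perspective together with a label that is too broad. The Analysis section announces provider costs and then uses payer plus patient payments. It calls those payments the cost to society and leaves the INB cost term without a perspective. Followed as written, it would support a societal conclusion that the calculation does not deliver.

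The effect on the INB is unknown in both size and direction. The verdict rests on two readings: that the sum consists of the components the sentence names, and that a societal cost is broader than payments for health care, at least by including patient and carer time. Severity is minor. This is a secondary economic analysis, and the one-month Roland and pain comparisons do not depend on it.

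**What to change.** In the Analysis section:

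1. State that the INB cost term is the payer plus patient cost of health care, with each dollar counted once.
2. Replace the reference to provider costs with that same term.
3. Report the INB and the acceptability curve as a health-care (payer plus patient) perspective, and drop the societal label for this total.
4. Optionally, add a sensitivity INB that values patient time at visits, using the visit counts and average lengths already collected. It needs an hourly value, which the article does not give. Describe the result as partial, since it still leaves out carer time and patient time outside visits, and do not call it a full societal cost.

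Items 1 to 3 are wording changes that need no new data and should be settled before the economic analysis is run. Item 4 is a small extra calculation. The price is a narrower headline claim.

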## Discussion

Although extensively utilized throughout North America for palliation of pain, vertebroplasty still has not undergone rigorous study. The study outlined above represents the first randomized, controlled study that can account for a placebo effect in the setting of vertebroplasty.

Waning enrolment caused the addition of foreign sites to the study to have the number of subjects needed for an acceptable sample. Approval was obtained from the State Department and the NIH and some foreign sites were initiated into the study and enrolment increased. We now anticipate enrolling a total of 100 subjects. Assuming a 90% follow up rate at one month, we maintain good power (80%) to detect group differences in Roland of 4.0 or more and 87% power for differences in pain of at least 1.75.

Results from this study should provide compelling evidence as to whether or not internal stabilization of non-healing, painful, osteoporotic vertebral compression fractures offers clinical benefit.

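### The model beyond 12 months is built only if one-year differences are significant, so whether a longer-horizon economic result exists, and how large it is, depends on an undefined test the trial is not sized for

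*Protocol article*

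**What the plan says.** All references are to the protocol article.

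- **Horizon (Analysis, economic paragraphs).** The base case is one year: "We believe that the 12-month time-frame will allow adequate measurement of the important differences in cost and outcome between treatment arms". The next sentence makes extrapolation conditional: "if significant differences persist at one year, we will construct a decision model to extrapolate the results". It does not say whether the difference meant is in EQ-5D, cost, Roland, pain or INB, and it gives no test or level.
- **Exploratory model (same paragraph).** A worst-case model assumes that "any benefits of vertebroplasty fall off rapidly over time such that after 5 years benefits are equal between groups". This sentence has no condition of its own, and the text does not say whether it is run when the preceding condition fails. On discounting: "All costs and benefits beyond one year will be discounted at 3%, according to U.S. guidelines".
- **Effect measure and decision framework (Analysis).** "The primary economic outcome measure is the EQ-5D preference score". Results are expressed as INB and as a bootstrap CEAC, used "to determine, for any given willingness-to-pay cut-off, the probability that vertebroplasty is cost-effective", in deliberate preference to one cut-off.
- **Size.** Sample Size and Discussion give power only for Roland and pain, and Analysis sets the primary time point at one month. The current expectation is in the Discussion: "We now anticipate enrolling a total of 100 subjects".
- **Losses and crossover.** Data Management expects 15% withdrawal by one month and a further 10% by one year. Crossover opens after the one-month assessment (Crossover section), and Analysis accepts that this may dilute intention-to-treat effects.

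**The concern.** A rule that builds a model only after a significant result has two effects.

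1. When a real one-year difference is missed because the trial is small, no extrapolated result follows under this rule. At this sample size, non-significance is weak evidence that benefit does not last.
2. When the test passes, the estimate has been selected for being large. Projecting it forward multiplies the excess over later years, and a bootstrap run only after the condition is met does not by itself show that selection.

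The rule also sits badly with the plan's own reasoning. The CEAC was chosen so that decision-makers see a probability at every willingness-to-pay value. A significance condition placed ahead of it brings a cut-off back in. Because the trigger is undefined, it could also be chosen after the one-year data are seen.

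What is at stake is the longer-horizon economic conclusion only.

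**Working it through.** **Inputs from the protocol.** Roland SD 6.7 and pain SD 2.7 (Sample Size); 100 subjects expected (Discussion); 15% + 10% withdrawal (Data Management).

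**Assumptions.** Two-sided alpha 0.05 (not stated, but it reproduces the stated powers); one-year SDs equal to the pilot SDs; EQ-5D SD 0.20 to 0.30 and true EQ-5D differences of 0.05 and 0.10 (the protocol gives neither).

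**Formulas** (normal approximation, n per arm):
- SE = SD × √(2/n); L = true difference / SE
- Chance of a significant result in the true direction: P = Φ(L − 1.96)
- Mean significant estimate ÷ truth = 1 + φ(1.96 − L) / (L × P)

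**Step 1: reproduce the plan's figures.**
- Roland, n = 75: 4 points 95.5% (stated 95%); 3 points 78.3% (stated 78%).
- Roland, n = 45: 4 points, SE = 6.7 × √(2/45) = 1.41, L = 2.83, P = 80.8% (stated 80%).
- Pain, n = 45: 1.75 points 86.8% (stated 87%).

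The stated powers are sound, but they concern one month.

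**Step 2: subjects left at one year.** 100 × (1 − 0.25) = 75, or 37.5 per arm.

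**Step 3: if Roland or pain is the trigger.** Roland SE = 6.7 × √(2/37.5) = 1.547; pain SE = 2.7 × √(2/37.5) = 0.624.

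| True one-year difference | L | Model triggered | Inflation |
|---|---|---|---|
| Roland 4 | 2.585 | 73% | 1.17 |
| Roland 3 | 1.939 | 49% | 1.42 |
| Roland 2 | 1.293 | 25% | 1.98 |
| Pain 1.75 | 2.807 | 80% | 1.12 |
| Pain 1.25 | 2.005 | 52% | 1.38 |

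Worked line, Roland 3: φ(1.96 − 1.939) = 0.399; 1 + 0.399 / (1.939 × 0.492) = 1.42. If crossover halved a 4-point effect, the 2-point row would apply.

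**Step 4: if EQ-5D is the trigger.** At SD 0.25, SE = 0.25 × √(2/37.5) = 0.0577, so only estimates beyond 1.96 × 0.0577 = 0.113 pass.

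| True difference | Model triggered (SD 0.20–0.30) | Inflation |
|---|---|---|
| 0.05 | 11–19% | 2.3–3.2 |
| 0.10 | 30–58% | 1.3–1.8 |

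These inflation figures average all significant results, including the rare wrong-sign ones. Counting only the true direction, the upper end for 0.05 is 3.4. At SD 0.25 and a true 0.05, the mean passing estimate is about 0.138.

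**Step 5: if one measure is tested and another carried forward.** Suppose Roland (4 points) is the gate and a true EQ-5D difference of 0.05 is projected. The Roland estimate is shifted by φ(1.96 − 2.585)/0.734 = 0.447 SE. The EQ-5D inflation is then 1 + r × 0.447 × 0.0577/0.05. For an assumed correlation r of 0.3 to 0.7 this is 1.15 to 1.36.

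**Step 6: what the condition switches on or off.** Take an assumed one-year gap g that falls linearly to zero at year 5, discounted at 3%, with mortality ignored. The integral from 1 to 5 of (1 − (t − 1)/4) × 1.03^−(t−1) is 1.92, so the gain after year one is 1.92 × g, or 0.096 QALY for g = 0.05. A faster decline (one-year half-life, assumed) gives about 1.31 × g.

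**The case against.** The other side has several good points, and most of them limit the scope.

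- **The 12-month result stands.** A reader might infer that a significance test decides the horizon of the whole economic evaluation, so that INB and CEAC jump between two values. The text does not support that. The 12-month analysis carries no condition, and nothing says the extrapolated result replaces it. A 12-month INB answers a shorter-horizon question and is not biased by the rule.
- **Later benefit is not necessarily set to zero.** The 5-year worst-case sentence has no condition and may be meant to run regardless. That is unclear either way. Even if always run, it changes how long benefit lasts, not the starting value.
- **The trigger is not named.** A reader might take a near threefold inflation as the headline. That figure needs EQ-5D as the trigger, a true gap of 0.05 and a 0.05 level, none of which is in the protocol. With large Roland or pain effects the inflation is 12–17%, and at the 166-subject target with 25% loss it is about 5% for 4 Roland points. The word used for the condition is not expressly called statistical, though no other threshold is offered.
- **Detail may sit elsewhere.** How uncertainty enters the model may be set out in the fuller plan. But the condition itself is stated here, so it is not merely an omission.

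What survives is a stated, undefined, data-dependent condition on the extrapolation, and upward bias in what passes it.

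**Conclusion.** The concern holds in limited form. Whether the extrapolation model is built depends on a one-year comparison that the trial was not sized for, and an estimate that passes is too large on average if it, or something correlated with it, is projected. The size runs from slight (1.12-fold, pain 1.75) through 1.4- to 2.0-fold (Roland 3 to 2 points) to 2.3- to 3.2-fold (EQ-5D 0.05, assumed SD). These figures rest on 37.5 per arm, two-sided 0.05 and one-year SDs equal to the pilot values. Severity is minor: the one-month co-primary tests and the 12-month INB and CEAC are untouched.

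**What to change.** - Keep the 12-month INB and CEAC as the base case.
- Delete the significance condition. Always run the extrapolation, including the 5-year worst-case scenario, from the estimated one-year difference whatever its p-value.
- Carry the bootstrap uncertainty of that difference into the extrapolated CEAC.
- Report the extrapolated result beside the 12-month one, labelled as secondary.

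The cost is about one sentence in the plan, with no new data and no change to conduct. The model must be built in every case, and the extrapolated result will show more uncertainty.
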